#### RQ1: NLP analysis

4.2.2

The spoken journal entries will be transcribed using Whisper [65]. All journal entries will be preprocessed according to standard NLP procedure (tokenization, lowercasing, lemmatization, and stop-word removal) to generate sparse representations [e.g., term frequency–inverse document frequency; TF–IDF). Additionally, dense representations (e.g., contextual embeddings from German pre-trained transformer-based models like GBERT [66] or German-BERT [67]] will be generated. Here, preprocessing will be limited to the model-specific tokenization procedure.

The comparison of architecture classes is itself part of the study, as prior literature has not yet established a best-performing architecture for journaling data. Therefore, different supervised machine learning models will be employed for this regression task, ranging from classical approaches (e.g., random forest regression or support vector regression) to transformer-based deep learning models (e.g., BERT-based regression head). Separate predictive models will be trained on the above-mentioned representations for each outcome variable (MDBF subscales, PSS-4). We will additionally evaluate end-to-end fine-tuning of a smaller transformer model (e.g., a distilled German BERT variant), which will operate directly on tokenized journal entries rather than precomputed representations. Here, we acknowledge the higher risk of overfitting compared to our main representation-based approach.

As a baseline, a mean predictor will be implemented. Model performance will be quantified using root mean squared error (RMSE) and mean absolute error (MAE) to capture prediction error magnitude, and Pearson correlation to assess the strength of association between predicted and observed scores. All models will be evaluated using k-fold cross-validation. To account for repeated measures within participants, cross-validation will be conducted at the participant level, such that all entries from a given participant are assigned exclusively to either the training set or the test set. To examine group differences, models will be trained and evaluated separately for the written and transcribed groups. Predictive performance metrics will then be compared across groups. Differences in performance will be formally tested using bootstrapped confidence intervals to provide robust inference without assuming normality of error distributions.

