#### RQ5: expert rating

4.2.6

The best-performing NLP model will be retrained with optimized hyperparameters on the full dataset, excluding the expert-rated entries. Model and expert performance will be compared on item-level absolute errors using RMSE, MAE, and Spearman’s ρ, with parametric or nonparametric pairwise tests applied as appropriate. Effect sizes and 95% confidence intervals will be reported, and bootstrap confidence intervals will supplement differences in MAE and RMSE.

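### RQ1 describes one cross-validation layer for many pipelines, does not keep selection and tuning inside the training folds, and states no inference against the mean predictor

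*Protocol article*

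**What the plan says.** Section 4.2.2 (RQ1: NLP analysis) of the protocol article leaves the set of candidates open: "different supervised machine learning models will be employed for this regression task, ranging from classical approaches" to transformer-based regression, on sparse and dense representations, plus end-to-end fine-tuning of a smaller transformer. Separate models are built for four outcomes: the three MDBF subscales and the PSS-4. Three metrics are listed (RMSE, MAE, Pearson correlation) and none is named as primary.

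The evaluation scheme is stated as "All models will be evaluated using k-fold cross-validation". The split is by participant: "all entries from a given participant are assigned exclusively to either the training set or the test set". No validation set, inner loop or untouched group of participants is mentioned. The reference is given as "As a baseline, a mean predictor will be implemented". Bootstrap intervals come directly after the sentences on comparing the typed and spoken groups.

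Section 4.2.6 (RQ5: expert rating) continues: "The best-performing NLP model will be retrained with optimized hyperparameters on the full dataset, excluding the expert-rated entries". Section 3.7 puts the expert-rated set at 24 entries. Section 2 ranks RQ1 first among the hypotheses and makes RQ1 and RQ2 together the condition for future work on automatic feedback.

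**The concern.** Retraining a best model with optimised settings means that a winner and its settings were fixed beforehand. The only earlier evaluation described is the single cross-validation of section 4.2.2. If those folds choose the pipeline or tune it, and the same folds supply the performance figure, that figure is the best of several noisy estimates and overstates performance on new participants.

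The error is small when prediction is good. It is most damaging when prediction is poor, which is where the RQ1 answer is in doubt. The plan implements a mean predictor but states no interval, margin or criterion against it. A selected model with a marginally lower error could therefore be read as showing that well-being can be predicted.

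RQ5 inherits the problem. The 24 expert-rated entries are left out of retraining, but nothing says they, or the participants who wrote them, are left out of choosing and tuning the model.

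**Working it through.** **Inputs from the protocol article.** Section 4.1: 500 data points per group, 14 days, 28% dropout. Section 4.2.2: participant-level k-fold cross-validation (k not given), an open list of pipelines, four outcomes, three metrics.

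**The plan's own figure.** N = D / (d × (1 − r)) = 500 / (14 × 0.72) = 500 / 10.08 = 49.6, rounded up to 50 per group. This reproduces. Fifty participants give 50 × 14 × 0.72 = 504 expected entries, about 10 each, so the simulations used 50 participants with 10 entries each.

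**Assumptions.** The article gives no intraclass correlation (ICC), number of pipelines or correlation between pipeline errors. These were varied over assumed ranges.

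**Simulation A: reporting the best of several equally good pipelines.** ICC 0.3 to 0.5; 6, 12 or 50 pipelines; error correlation 0.5 or 0.8; 600 runs per setting. Optimism = mean of the best r − mean r of a single pipeline.

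| True r | Smallest optimism | Largest optimism |
|---|---|---|
| 0 | 0.033 (6 pipelines, ICC 0.3, correlation 0.8) | 0.127 (50 pipelines, ICC 0.5, correlation 0.5) |
| 0.4 | 0.029 (6 pipelines, ICC 0.3, correlation 0.8) | 0.095 (50 pipelines, ICC 0.5, correlation 0.5) |

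With no signal, the chance that the best pipeline exceeds the 97.5% null limit of a single pipeline rises from 2.5% to between 7.0% and 34.7%.

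**Simulation B: selecting on the reporting folds (flat) against nested selection.** Ridge regression with 20 settings (4 feature-set sizes × 5 penalties), 5 participant-level folds, ICC 0.4, 200 runs per setting.

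| Signal | r flat | r nested | Difference | Lower RMSE than mean predictor, flat | Same, nested |
|---|---|---|---|---|---|
| None | 0.047 | −0.022 | 0.047 + 0.022 = 0.069 | 79% | 15% |
| Weak | 0.226 | 0.172 | 0.054 | 99% | 66% |
| Stronger | 0.487 | 0.468 | 0.019 | 100% | 100% |

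With no signal the mean RMSE was 0.997 flat, 1.009 nested and 1.002 for the mean predictor. The spurious wins are therefore narrow (1.002 − 0.997 = 0.005 on average). They count as wins only when point estimates are compared without an interval, and an interval against the mean predictor is what the plan does not state.

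**The case against.** The strongest reply is that the article never says the RQ1 folds pick a winner, tune it or supply a headline score. The best-model wording appears only under RQ5, which is exploratory. A condensed article may leave inner loops and tuning grids to a fuller plan that is not shown. Comparing architectures is a declared aim ("The comparison of architecture classes is itself part of the study"), and if every architecture is reported there is no winner-only result. Splitting by participant is correct and already prevents leakage within persons.

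Much of this stands, and it makes the point conditional. A reader might infer that the plan commits to selecting and reporting on the same folds; the text neither says so nor excludes nesting. But the article does set out the split unit, the partitions, the metrics, the baseline and the bootstrap. At that level of detail it describes one layer plus a best-model step, and leaves selection and tuning no other data. Reporting all architectures reduces winner bias but does not remove the bias from tuning each one on its own test folds.

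Two stronger readings are not supported:

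- **Unequal bias between typed and spoken groups.** With the same candidates and procedure in both groups the optimism is largely shared. Bias in the difference was not simulated, and the article does not say that the groups will be compared on different architectures.
- **An inflated family-wise error over outcomes and metrics.** The article states no significance tests of predictability, outcome by outcome and metric by metric, to which such a rate would apply.

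Nor is RQ1 without any reference, since the mean predictor is there. What is missing is inference against it.

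**Conclusion.** The point holds in conditional form. Followed as written, sections 4.2.2 and 4.2.6 do not keep selection and tuning inside the training folds. If the score of a selected or tuned model on those folds is reported as RQ1 performance, it overstates Pearson r by about 0.02 to 0.13 under the assumed settings. With a clear signal the conclusion hardly changes. With little or no signal the model can appear to beat the mean predictor when it does not. The direction was the same in every setting tried; the size depends on the assumed ICC, number of pipelines and error correlation.

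Separately, the first-ranked hypothesis has a baseline but no stated inference against it. The bootstrap sentence might be stretched to cover this, but its position ties it to the group comparison.

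**What to change.** 1. State that all choice of representation, architecture and hyperparameters is made in an inner participant-level loop. Report performance from the outer loop, with the same procedure in both groups.
2. Show the per-architecture table as descriptive.
3. Name one outcome and one metric in advance for RQ1. Give a bootstrap interval, resampling participants, for the error reduction over the mean predictor, and judge predictability on that interval.
4. For RQ5, keep the participants behind the 24 expert-rated entries out of model selection and tuning as well as excluding those entries from retraining.

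The cost is a few sentences, more computing time on a small dataset and slightly lower reported accuracy. The target of 50 participants per group is unchanged. Step 4 withholds at most 24 participants from model selection and tuning for RQ5, and fewer if some contribute more than one rated entry.

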### Procedure

3.3

Upon completion of enrollment, participants will be welcomed by the study team within the app and prompted to complete the baseline assessment questionnaires. For this purpose, they will receive an individualized link via the messenger service to an online survey hosted on the SoSci Survey platform^2^, which can be accessed through their smartphone browser. The link will contain each participant’s unique code to ensure accurate data assignment. The survey will cover demographics, education, general well-being, mental health, stress, and dispositional self-control, and is expected to take no longer than 10 to 15 min to complete. Subsequently, participants will be randomized into two groups using block randomization with randomly varying block sizes of 4, 6, and 8 to ensure approximately equal distribution. To generate the list of group assignments, the tool Sealed Envelope [48] is used. Participants are then assigned based on their registration sequence. The type group will be instructed to consistently type their journal entries, whereas the speak group will be instructed to record their journal entries as voice messages via the messenger service. In order to establish a “neutral voice” baseline for each participant in the speaking group, they will be asked to read standardized text snippets from the literature on voice assessment.^3^ These snippets are designed to avoid eliciting emotion or cognitive load.

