### Sample size calculation

4.1

In this NLP study, classical power analysis is not directly applicable, as the model performance depends on several factors such as training data points, model architecture, and transfer learning effects. Therefore, based on preceding transfer learning literature, 500 data points (D) per group (type and speak) are targeted [60, 61]. Each participant is expected to contribute one data point daily over the study duration of 14 days (d). A dropout rate of 28% (r) is assumed based on comparable studies [62–64]. The number of participants is calculated to be 50 participants per group (100 total):$$N=\frac{D}{d\times (1-r)}=\frac{500}{14\times (1-0.28)}\approx 49.6\approx 50$$

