To maximize adherence, the participants should have the option to receive their notifications at individually chosen times. If this is not possible, a reminder closer to the common bedtime should be chosen. Furthermore, in order to investigate differences in speaking and typing, participants are randomly assigned to either the typing or speaking group. Allowing participants to freely choose their group is recommended to reduce early dropout before the study begins and to improve the journaling experience, as individuals are likely to differ in their preferred mode of expressing thoughts and emotions. This recommendation is consistent with previous studies advocating for personalized settings in mobile health applications [21]. Moreover, in cases of excessive smartphone use, participants may express a desire for off-screen time and a preference for pen-and-paper journaling over digital journaling. A potential future application could therefore involve offering pen-and-paper journaling in combination with a text recognition tool to capture journal content from photographs. Beyond this, alternative input modalities such as video recordings, drawings, or other creative formats could be considered to broaden accessibility and better accommodate individual preferences.

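### The RQ1 typed-versus-spoken contrast names no deciding metric, and its RMSE and MAE are not scaled to each group's own outcome spread

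*Protocol article*

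**What the plan says.** Section 2 of the protocol article puts a directional hypothesis under RQ1: accuracy is expected to be higher for transcribed speech than for typed text. Section 4.2.2 sets out the comparison: "models will be trained and evaluated separately for the written and transcribed groups. Predictive performance metrics will then be compared across groups". Three metrics are listed: RMSE, MAE and the Pearson correlation of predicted with observed scores. Cross-validation is by participant, a mean predictor serves as baseline, and group differences are tested with bootstrapped confidence intervals. No metric is singled out for the modality question, and the baseline is not linked to the group contrast.

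The groups are meant to be equal. Section 3.3 uses "block randomization with randomly varying block sizes of 4, 6, and 8 to ensure approximately equal distribution". In Section 4.1, "500 data points (D) per group (type and speak) are targeted", and one common loss rate applies: "A dropout rate of 28% (r) is assumed based on comparable studies". Under Section 4.3.1, days lacking either the journal or the questionnaire are dropped without imputation. Section 4.2.4 models compliance with group as a fixed effect, and Section 4.2.5 explores whether mood and stress develop differently by group.

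**The concern.** RMSE and MAE measure error in questionnaire points. When a model explains a modest share of the variance, most of its RMSE is simply the standard deviation of the scores being predicted. Here the two RMSEs come from two different sets of people. A group with more variable mood will show larger errors even if its texts are just as informative.

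Randomisation makes the expected spread equal at entry, but with about 50 people per group the realised spread can differ noticeably. That noise falls on two of the three planned metrics. If the metrics then point in different directions, the article gives no rule for which one answers the hypothesis. A systematic difference in spread, through an effect of modality on reported mood or through group-dependent loss of entries, would turn the noise into bias. The plan itself examines both routes (Sections 4.2.4 and 4.2.5). At stake is the modality half of the primary research question.

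**Working it through.** **Inputs from the document.** D = 500 entries per group, d = 14 days, r = 0.28 (Section 4.1); 1:1 block randomisation (Section 3.3). **Assumed, because the document gives no value:** ICC of daily scores 0.3 to 0.5; R² between 0.10 and 0.40.

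**1. The plan's own figure.** N = D / [d(1 − r)] = 500 / (14 × 0.72) = 49.6, so 50 per group and 100 in total. This reproduces. Expected entries are 50 × 14 × 0.72 = 504 per group.

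**2. How much a real gain moves RMSE.** For calibrated predictions, RMSE = SD × √(1 − R²).
- R² 0.10 to 0.20: √(0.80/0.90) = 0.943, a fall of 5.7%.
- R² 0.20 to 0.30: √(0.70/0.80) = 0.935, a fall of 6.5%.

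**3. How much spread differs by chance.** Simulated ratio of outcome SDs between two groups drawn from one population:

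| ICC | People × entries | 95% range of ratio | Median gap |
|---|---|---|---|
| 0.3 | 50 × 10 | 0.89 to 1.13 | 4.0% |
| 0.5 | 50 × 10 | 0.85 to 1.18 | 5.4% |
| 0.3 | 36 × 14 | 0.88 to 1.14 | 4.6% |
| 0.5 | 36 × 14 | 0.84 to 1.19 | 6.1% |

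A separate simulation with 50 people and 14 days at 72% completion gave about 0.84 to 1.19 for the mean-predictor RMSE. The chance range is thus wider than the effects in step 2.

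**4. A reversal by hand.** SD 1.0 with R² 0.20 gives RMSE √0.80 = 0.894. SD 1.1 with R² 0.30 gives 1.1 × √0.70 = 0.920. The group with the better prediction has the larger RMSE.

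**5. How often the ranking is wrong.** For true R² of 0.10 against 0.20 (50 people, 14 days at 72% completion, ICC 0.3 to 0.5), the better group ranked worse in:
- 22–26% of simulated trials on RMSE;
- 5–12% on R² against the mean predictor;
- 4–10% on Pearson r.

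A second run, with prediction errors not clustered by person, gave 21–23% on RMSE and about 3% on R². In that run, across this contrast and 0.20 against 0.30, RMSE ranked the groups wrongly while Pearson r ranked them correctly in 14–23% of trials.

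**6. Does scaling remove the artefact?** Ridge regression with 5-fold participant-level cross-validation (100 features, true R² 0.4, ICC 0.4, all assumed; 50 people × 10 entries):
- SD 1.00: RMSE 0.854, skill 0.271, r 0.51.
- SD 1.15: RMSE 0.985, skill 0.271, r 0.51.

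RMSE is 0.985/0.854 = 1.15 times as large, while skill and r do not move. With no true difference between groups, the log RMSE ratio correlated 0.78 with the log SD ratio.

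**7. Training size.** In the same model, 600, 500, 400 and 300 entries gave skill of 0.29, 0.27, 0.24 and 0.21. Going from 500 to 400 raised RMSE from 0.854 to 0.873 (about 2%) and lowered r from 0.51 to 0.48. With 28% loss in both groups and all-or-none dropout, the chance gap in entries has a median of 42 and a 95th percentile of 126. Completion of 80% against 64% would give 700 × 0.80 = 560 against 700 × 0.64 = 448.

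**The case against.** Several points on the other side stand.

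- **Pearson r is already planned** and does not change under linear rescaling. In step 5 it did as well as the skill score. The units problem therefore touches two of the three metrics.
- **Chance spread is sampling error, not bias.** With 50 people × 10 entries, assumed ICC 0.4 and R² 0.15 in both groups, a bootstrap by participant covered a null RMSE ratio about 93% of the time, against 79% for a bootstrap by entry. The article does not state the resampling unit. A participant-level interval would be honest but wide, and no bootstrap removes a systematic difference. The rates in step 5 count signs of point estimates, which is not the planned decision rule.
- **A skill score is not immune to spread.** The simulations fix R² as the truth, which favours R². If error is constant in scale units, say RMSE 0.90 in both groups, SD 1.00 gives 1 − 0.81/1.00 = 0.19 and SD 1.15 gives 1 − 0.81/1.3225 = 0.39. This is why raw errors and SDs must stay in view.
- **Some detail may sit in an analysis plan that is not shown.** That is fair for down-sampling and learning curves. The group contrast and its metrics, however, are stated in the article.

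A reader might infer that the modality answer will largely reflect group spread and unequal training data. The document does not support that. It plans equal groups and equal entry counts, training size had the smaller effect, and without a stated SD, ICC or expected R² the share due to spread cannot be known. A reader might also take the Discussion's remark, "Allowing participants to freely choose their group is recommended to reduce early dropout before the study begins", as evidence that loss differs between typing and speaking. It concerns choice of group and dropout before the start, and says nothing on differential loss during the 14 days.

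**Conclusion.** The point holds in a limited form. The RQ1 modality contrast has no deciding metric, and two of its three metrics carry a nuisance quantity that, at 50 people per group, can vary by chance more than a plausible modality effect: a ratio of up to about 0.85 to 1.18, against a 5.7% change in RMSE for R² 0.10 to 0.20. The consequences are lost precision on RMSE and MAE, possible conflict with Pearson r that the article does not resolve, and bias only if spread differs systematically by modality or dropout. Unequal training size is a contingent and lesser risk. The sizes rest on assumed ICC and R² values; the direction of the argument needs only that RMSE and MAE scale with the outcome SD. The sample size figure is not in question. This is a worthwhile, low-cost improvement to a primary comparison, not a fatal defect.

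**What to change.** In Section 4.2.2, or in the analysis plan before the data are analysed:

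1. Name one deciding between-group contrast: skill against the mean predictor fitted in the same folds of the same group, either 1 − MSE/MSE_mean or 1 − MAE/MAE_mean. Report Pearson r beside it.
2. Keep raw RMSE and MAE as description, with each group's outcome SD, so that a reader can see whether a skill difference comes from smaller errors or from wider spread.
3. If realised entry counts differ clearly between groups, add a sensitivity analysis with training size matched. Scaling alone does not remove that effect.

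The denominator comes from a baseline that the plan already implements, and no new data are needed. The cost is a few sentences and some extra computation. The matched analysis, if it is triggered, uses fewer entries from the larger group, so the full-data result should stand next to it.

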## Research questions and hypotheses

2

Building upon the illustrated gaps in current research, this study investigates the potential of NLP applied to digital journaling data with the aim of monitoring and supporting students’ emotional well-being, while generating individualized feedback on the journaling content and evaluating the students’ preferences.

Primarily, we hypothesize that (RQ1) emotional well-being and stress levels can be predicted from journaling entries using NLP. Prediction accuracy is expected to be higher for spoken entries (transcribed speech) compared to typed entries. Secondly, we hypothesize that (RQ2) the participants will evaluate the individualized feedback positively, indicating its acceptability and potential to foster reflection and compliance. Thirdly, we expect (RQ3) higher *state self-control* and *trait self-control* to be associated with greater adherence to the study protocol, and will be negatively correlated with dropout rates.

Furthermore, we will undergo (RQ4) an exploratory analysis of the improvement of the students’ emotional well-being over the study period, including the difference when typing vs. speaking the journal entries. Lastly, (RQ5) the predictive performance of NLP models will be compared to that of human experts (psychotherapists and clinical psychologists) in an exploratory manner to gain a practical perspective on the models’ performance. If RQ1 and RQ2 should hold true, future work should proceed to explore the usage of NLP to provide feedback automatically.

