### Design

3.1

The study is a two-week observational study with an exploratory approach that uses NLP to explore the applicability of NLP-based analyses of journal entries for monitoring students’ emotional well-being and giving individual feedback. For this purpose, we will analyze the usage of spoken vs. typed journal entries for identifying mood and stress and determine which types of feedback are favored. In more detail, the study will investigate which type of input modality performs better in predicting the students’ emotional well-being using self-labeled journaling entries as ground truth. An overview of the study design is shown in Figure 1; further procedural details are provided in Section 3.3.

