## Discussion

5

This study is the first to examine the effectiveness of NLP-based analyses of journal entries for monitoring and reflecting students’ emotional well-being. The study will investigate (RQ1) whether spoken vs. typed journaling entries influence the monitoring of emotional well-being and (RQ2) which types of feedback are preferred by students. To this end, it will be assessed which input modality is better suited to predict students’ emotional well-being and stress, with self-annotated journal entries serving as ground truth. We hypothesize that students’ emotional well-being can be predicted from journaling entries using NLP, with higher predictive accuracy for spoken compared to typed entries. We further expect that stress levels can be predicted from journaling entries, and that participants will evaluate the individualized feedback positively.

Owing to the messenger-based guidance provided throughout the study period, the individualized feedback on participants’ data, and the monetary incentives offered, high compliance is anticipated, thereby facilitating the collection of the data required for training the NLP models. In cases of temporary demotivation, participants may additionally be re-engaged through personalized messages, helping to maintain sustained participation over the course of the study. Furthermore, the provision of a low-threshold, fully online study—independent of location and infrastructure and accessible to everyone—addresses the challenge of potential bias from non-representative samples limited to non-rural areas. Ethical approval and the implementation of a robust data protection concept constitute essential prerequisites for ensuring participant trust and compliance.

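### RQ1 formally tests spoken against typed entries over four outcomes, several model types and three metrics, with no deciding contrast and no family-wise error control

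*Protocol article*

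**What the plan says.** - **Status of the hypothesis.** Protocol article, section 2: "Primarily, we hypothesize that (RQ1) emotional well-being and stress levels can be predicted from journaling entries using NLP". The next sentence adds the modality claim: "Prediction accuracy is expected to be higher for spoken entries (transcribed speech) compared to typed entries". In that section only RQ4 and RQ5 are labelled exploratory.
- **Outcomes.** Section 4.2.2: "Separate predictive models will be trained on the above-mentioned representations for each outcome variable (MDBF subscales, PSS-4"), which makes four.
- **Models.** Section 4.2.2 plans classical learners and transformer regression heads on sparse and dense representations, plus an end-to-end fine-tuned smaller transformer. Comparing architectures is itself an aim. The representation-based approach is called the main one, but it covers several representations and learners.
- **Metrics.** RMSE, MAE and Pearson correlation; none is given priority.
- **Test.** Section 4.2.2: "Differences in performance will be formally tested using bootstrapped confidence intervals". No interval level is given there; 95% appears only under RQ5 (section 4.2.6).
- **Design label.** Section 3.1: "The study is a two-week observational study with an exploratory approach".
- **Scope of the directional claim.** In section 2 it follows a sentence covering both well-being and stress. The abstract's expected results mention well-being only. Section 5 plans to assess modality for both, states the spoken advantage for well-being, and then adds: "We further expect that stress levels can be predicted from journaling entries".

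**The concern.** A directional primary hypothesis that is to be formally tested needs a defined test. Here at least four contrasts qualify, one per outcome, and more if the comparison is made for several models or metrics. They can disagree: speech could do better on valence under one pipeline and worse on calmness under another. Nothing in the article says which result settles the modality part of RQ1, or whether one favourable outcome is enough or all are required. The answer could therefore be chosen after seeing which contrast separates the groups, and a claim resting on one unadjusted interval would carry more than its nominal error. The exploratory label in section 3.1 would excuse this, but it conflicts with the primary status in section 2 and the formal test in section 4.2.2.

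**Working it through.** **The plan's own figure.** The article gives no error rate or power for RQ1. Its only related number is the sample size in section 4.1: 500 / (14 × (1 − 0.28)) = 500 / 10.08 = 49.6, rounded to 50 per group. This reproduces, but it sets a data volume and says nothing about the modality contrast.

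**Inputs from the article.** Four outcomes; three metrics; number of models not fixed.

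**Inputs assumed.** Each interval is a valid two-sided 95% interval (critical value 1.96). Any one interval excluding zero counts as a difference. Contrasts are jointly normal with equal correlation r between outcomes. There is no true modality difference.

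**Step 1: four outcomes, one model, one metric.** If independent, either direction: 1 − 0.95⁴ = 0.185. Spoken better only: 1 − 0.975⁴ = 0.096. Correlated cases are by simulation:

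| r between outcomes | Either direction (benchmark 5%) | Spoken better (benchmark 2.5%) |
|---|---|---|
| 0 | 18.5% | 9.6% |
| 0.5 | 15.5% | 7.8% |
| 0.7 | 13.0% | 6.5% |
| 0.8 | 11.4% | 5.7% |
| 0.9 | 9.4% | 4.7% |

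**Step 2: the test repeated over models.** Outcome correlation 0.5, one metric; the number of pipelines and their correlation are assumed:

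| Pipelines | r between pipelines | Either direction | Spoken better |
|---|---|---|---|
| 3 | 0.9 | 25% | 12% |
| 3 | 0.8 | 29% | 14% |
| 3 | 0.5 | 36% | 18% |
| 5 | 0.8 | 36% | 18% |

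**Step 3: three metrics as well.** With three pipelines, outcome correlation 0.5 and metrics correlated 0.8, the either-direction rate is about 43% (pipelines correlated 0.9) to 58% (0.5).

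**Step 4: the decision rule matters as much as the count.** If each outcome alone had 80% power and r = 0.5, an any-of-four rule would succeed 97% of the time and an all-four rule 56%. An all-four rule would not inflate the error at all.

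**Step 5: effect of adjusting.** Bonferroni over four outcomes uses 0.05 / 4 = 0.0125 each, critical value 2.50. Family-wise error becomes 1 − (1 − 0.0125)⁴ = 4.9% if independent, 4.3% at r = 0.5 and 3.7% at r = 0.7. Intervals widen by 2.50 / 1.96 = 1.27, that is 27%.

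**The case against.** The strongest reply is that the article describes the study as a "two-week observational study with an exploratory approach", disclaims a power analysis in section 4.1, and may leave the choice of outcome and any multiplicity rule to an analysis plan that is not shown. Silence on those details would not by itself be a fault. What remains is a conflict in the published text: one section says exploratory, another makes the hypothesis primary and directional, and a third announces a formal test. An unseen plan does not reconcile those statements.

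Four stronger readings are tempting and are not supported:

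- **That a spoken-better claim has a 16% to 36% false chance.** Those are either-direction rates. At the same settings the hypothesised direction has about half, 8% to 18%, against 2.5%. The upper end also needs a number of pipelines that the article does not give.
- **That the test will be run for every architecture.** Section 4.2.2 says that performance metrics are compared between groups; it does not say that each model gets its own formal test. Repetition over models is a possibility the text leaves open.
- **That the article flatly contradicts itself on stress.** Section 5 also says modality will be assessed for both well-being and stress, which agrees with section 2. Only the directional expectation is worded differently.
- **That the follow-on recommendation hangs on modality.** Section 2 says "If RQ1 and RQ2 should hold true, future work should proceed to explore the usage of NLP" for automatic feedback. RQ1 also includes predictability as such, and the abstract's discussion ties future work to engagement and predictive performance without a modality condition.

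**Conclusion.** The point holds in a limited form. The modality contrast is presented as a formally tested, directional part of the primary hypothesis, yet the article fixes neither the deciding contrast nor any family-wise control, and its exploratory label pulls the other way. The firmest estimate uses the four outcomes alone: a 9% to 18.5% chance of some false difference and about 5% to 10% of a false spoken-better result, from r = 0.9 to independence. Repetition over models or metrics would raise this, for example to 25% to 36% in either direction with three to five assumed pipelines. All of these figures rest on an assumed 95% level and an assumed any-one-counts rule. They show the scale of the risk if the plan is read that way; they are not error rates the plan commits to. The correction is worth making, and it does not affect the question of whether well-being can be predicted at all.

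**What to change.** In section 4.2.2, choose one of two routes.

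1. **Keep the formal test.** Name one metric and one pipeline from the main representation-based approach, the same in both groups and chosen without reference to the typed-spoken difference. State the outcome family and the interval level. Control the family at two-sided 5% with Holm or joint (max-T) bootstrap intervals. Limit the modality claim to outcomes whose adjusted interval excludes zero, and name them in the claim. Report the remaining architectures, metrics and contrasts as exploratory.
2. **Drop the formal test.** Label the whole modality comparison exploratory, in line with section 3.1, and amend section 2 so that it is not part of the primary hypothesis.

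Under either route, make the abstract, section 2 and section 5 agree on whether the expected spoken advantage includes stress; under the first, that settles whether PSS-4 is in the family.

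The cost is wording, with no new data. Under the first route, intervals for four outcomes are up to 27% wider and modality statements for the other architectures become descriptive. Under the second, the study can no longer claim to have tested the modality hypothesis.
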